**Methods/design:**

This study is a multicentre, non-inferiority randomized single blinded study. The study population consists of female patients with histological proven residual/recurrent CIN after previous surgical treatment. Four hundred thirty-three patients will be included in the Netherlands. The first 35 patients will be included in a pilot study to prove non-futility.

Included patients will be randomized to receive either 5% imiquimod cream or LLETZ treatment. Imiquimod will be inserted three times a week intravaginally for a period of 16 weeks using a vaginal applicator. Ten weeks after the end of imiquimod treatment a biopsy will be taken for treatment response. In case of progressive or stable disease a LLETZ will be performed. At 12 and 24 months after the start of treatment cytology will be taken for follow up. The LLETZ group will be treated according to the current guidelines. Throughout the study, HPV typing and quality of life will be tested.

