### Sample size calculation

The regression rate of a second LLETZ procedure is estimated 63% in a retrospective cohort (data not published). The regression rate of CIN lesions after treatment with imiquimod was based upon the only study reporting on the regression rate after 16 weeks of imiquimod therapy of primary CIN. This study showed a regression rate of 73% in patients with primary CIN lesions [23]. Since the effect could be lower in patients with residual or persistent CIN, we estimated the regression rate to be 60%.

To calculate the required sample size in this two-proportions non-inferiority trial we assume that the probability of regression is 63% for the standard (LLETZ procedure) while it is 60% after treatment with imiquimod.

Using a non-inferiority margin of 10% for the difference in proportions and a significance level (alpha) of 5%, a sample size of 174 per group is required to obtain a power of at least 80%. Allowing for 20% loss to follow-up the total required sample size is 433.

Because the uncertainty in the assumptions an interim analysis for futility will be performed by the Data Monitoring Committee (DMC) as soon as the primary outcome is available for 35 patients. This interim analysis is based on predictive power. That is the predicted probability of being able to prove non-inferiority given the results at the interim analysis. When the predictive power at this point is below 20% the trial will be stopped due to futility. Of course the DMC can always stop the trial due to safety concerns. The trial will never be stopped prematurely for efficacy so no alpha-adjustment is made.

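### The stated power of at least 80% takes no account of the firm futility stop at 35 outcomes, which lowers it to about 71–73% in the only set-up that reproduces 174 per group

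*Protocol article*

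**What the plan says.** All of this is in the protocol article; most of it is in Methods, Sample size calculation.

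- Planning rates: "we assume that the probability of regression is 63% for the standard (LLETZ procedure) while it is 60% after treatment with imiquimod".
- Margin and level: "Using a non-inferiority margin of 10% for the difference in proportions and a significance level (alpha) of 5" per cent.
- Size and power: "a sample size of 174 per group is required to obtain a power of at least 80" per cent, and then "Allowing for 20% loss to follow-up the total required sample size is 433".
- Interim look: the monitoring committee examines futility when 35 patients have a primary outcome. Predictive power is defined as the predicted chance of proving non-inferiority given the interim results. The rule is "When the predictive power at this point is below 20% the trial will be stopped due to futility".
- Consequence discussed: "The trial will never be stopped prematurely for efficacy so no alpha-adjustment is made". Nothing is said about power.

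Statistical methods defines proof of non-inferiority: the upper bound of a 95% Agresti interval for LLETZ minus imiquimod must lie below 10%. The Abstract describes the look more strongly: "The first 35 patients will be included in a pilot study to prove non-futility". Setting and study population makes the multicentre roll-out depend on passing it.

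**The concern.** A futility rule that is obeyed can only lower power, because some trials that would have succeeded are stopped. The article is right that such a rule needs no alpha adjustment, since it cannot raise the type I error. The cost falls on power, and the article is silent there.

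The look is very early. With 17 or 18 patients per arm the standard error of the difference is about 16 points, against a margin of 10, so the decision depends largely on chance. If the printed 80% leaves the rule out, the sponsor, the ethics committee and the monitoring committee are relying on a power that the design does not have. For the same reason, passing the look is weak evidence that the trial is not futile.

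**Working it through.** **Inputs.** From the article: rates 63% and 60%, margin 10 points, 174 per group, look at 35 outcomes, threshold 20%, success if the upper 95% bound is below 10%. Assumed: final n of 174 per group; interim split 17/18 or 18/17; independent Beta(1,1) or Beta(0.5,0.5) priors; Agresti interval read as Agresti–Caffo (one success and one failure added per arm).

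**1. Reproduce 174.** The variance sum is 0.63×0.37 + 0.60×0.40 = 0.4731, and n = (z_α + z_β)² × 0.4731 / d², where d is the distance from the true difference to the margin.

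- One-sided 5%, d = 0.13 (imiquimod 3 points better): (1.645 + 0.842)² × 0.4731 / 0.0169 = 173.07, so 174. Then 2 × 173.07 / 0.8 = 432.7, so 433. Both printed figures are matched.
- As stated, with imiquimod 3 points worse, d = 0.10 − 0.03 = 0.07. This needs 597 per group at one-sided 5%, or 758 at one-sided 2.5%.

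So 174 and 433 are fixed-sample numbers, and power with no look is 80.2% by this formula. Nothing has been added for the stop.

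**2. How early the look is.** Information fraction t = 35/348 = 0.10. Standard error = √(0.4731/17.5) = 0.164.

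**3. Normal approximation, flat prior.** Predictive power is below 20% when Z_t < z_α√t − 0.842√(1−t).

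- One-sided 5%: 1.645×0.317 − 0.842×0.948 = −0.277. The trial stops if LLETZ leads by more than 0.10 + 0.277×0.164 = 0.145, which is between two and three patients out of 17.5 per arm. With imiquimod 3 points better, the final Z has mean 0.13/√(0.4731/174) = 2.493. P(stop) = Φ(−0.277 − 2.493×0.317) = 14.3%. Bivariate normal power with the rule is 71.0%.
- One-sided 2.5% (the 95% interval), 63% versus 60%: the boundary is −0.177 and the mean is 0.07/0.0521 = 1.342. P(stop) = Φ(−0.177 − 1.342×0.317) = 27.4%. Power falls from 26.8% to 22.8%.

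**4. Exact enumeration.** Every interim table is listed, predictive power is beta-binomial, and the final test is the Agresti–Caffo bound. Ranges are over the priors and splits above unless noted.

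| Set-up | P(stop) | Power, no look | Power with rule |
|---|---|---|---|
| 174 per group, imiquimod +3, one-sided 5% | 12–15% | 80.4% | 71–73% |
| 174 per group, 63% v 60%, 95% interval | 29–31% | 26.8% | about 22% |
| 597 per group, 63% v 60%, one-sided 5%, flat prior | 13–17% | 80.6% | 68–72% |
| 758 per group, 63% v 60%, 95% interval, flat prior | 14–18% | 80.1% | 67–70% |

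At 63% v 60% with 174 per group and one-sided 5%, P(stop) is 21–25%. In the last two rows the 17 LLETZ/18 imiquimod split gives the larger loss (stop about 18%, power 67–68%); the reverse split gives the smaller.

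**5. Imiquimod truly at the margin (63% v 53%), 174 per group, 95% interval.** P(stop) is 46–48%, so 52–54% of such trials pass the look.

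**The case against.** **The 29% looks worse than it is.** A reader might set the 29–31% stop probability against the stated 80% and infer that nearly a third of an 80%-powered trial is thrown away. The documents do not support that. The 29–31% belongs to 63% versus 60% with the 95% interval, where power without any look is only 26.8%. With a flat prior the loss there is 26.8 − 22.4 = 4.4 points out of about 29 points of stopping, so about 85% of the stopped trials would have failed anyway. Much of that stop rate comes from the sample-size error. This objection stands, and the figures must be kept apart by set-up.

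**The look has a purpose.** The planning rates are uncertain: 63% is unpublished and 60% is extrapolated from primary CIN. The look is a gate before roll-out beyond two hospitals, and an early gate limits exposure and cost. This stands as a reason for having the look. It does not justify leaving its cost out of the power.

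**An article leaves detail to the full protocol.** The missing prior and operating characteristics are therefore not criticised. But the threshold, the timing, the firm wording and the 80% are all printed together, and 174 and 433 match the no-look calculation exactly.

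**A later look is not clearly better.** One might infer that the look must move. At 120 outcomes with the 20% threshold, P(stop) at 63% versus 60% rises to 37.5% (flat prior, 174 per group, 95% interval). At 120 with a 10% threshold it is still 24%. Later timing mainly buys more stopping at the margin and delays the gate. It is a trade-off, not a correction.

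**Conclusion.** The point holds in this form: the stated power of at least 80% ignores a firm stopping rule in the same section. In the only set-up that yields 174, power net of the rule is about 71–73%, a loss of roughly 7 to 9 points. Correcting the direction of the 3-point difference and the alpha level does not remove the problem: a trial sized for 63% versus 60% would lose about 9 to 13 points (flat prior). The claim that the pilot can prove non-futility is also too strong, since a treatment exactly at the margin passes more than half the time.

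The size depends on the assumed prior and split, which is why ranges are given, and on the rule being followed as written. If the committee treated it as advisory, the loss would be smaller. The point does not show that 29% of adequately powered trials would be wrongly stopped, or that a look at 35 is untenable.

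**What to change.** 1. Correct the sample-size calculation first; the figures for the rule depend on the final n and the alpha level.
2. State the power net of the futility rule, with the prior used, and give the stop probability at the planning rates, at equal rates and at the margin. If 80% net power is wanted, the sample size must rise to cover the loss. Otherwise this costs a short calculation and a few sentences.
3. In the Abstract, and in Setting and study population, describe the look as a futility check, not as proof of non-futility. This costs nothing.
4. Optional: keep the look at 35 as the gate before roll-out but lower the threshold to about 10%. The power loss is then about 3 to 5 points where power without the look is 70–80% (flat prior). The price is fewer stops when imiquimod is truly at the margin: about 27–30% with a 17/18 split, and as low as 23% with the reverse split, instead of 46–48% (174 per group, 95% interval). This needs an amendment and the monitoring committee's agreement.

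Whether to look later is for the sponsor to weigh.

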### Randomization

Randomization is performed by use of a computerized randomization tool, to prevent selection and allocation bias.

### Blinding

The study is single blinded: the pathologists evaluating cytological and histological samples are blinded with respect to the intervention.

### Data collection

The coded data will be stored both on paper and in an electronic database. A digital case report form (e-CRF) is used. The data is accessible only to the principal and coordinating investigator. The following data are recorded:

#### Baseline (all patients)

Patient characteristics: age, medical history, desire to have children, smoking, sexual behaviour.HPV genotypeQuality of life for both treatment groups.

#### 6 weeks follow-up

Adverse effects of imiquimod treatment: patient reported side effects and side effects noticed at clinical investigation.Adverse effects of LLETZ treatment: patient reported side effects.

#### 10 weeks follow-up

Treatment compliance: amount of applied doses of imiquimod for the imiquimod group.Adverse effects of imiquimod treatment: patients reported side effects and side effects noticed at clinical investigation.Colposcopy with biopsies to determine progressive or invasive disease in the imiquimod group.

#### 16 weeks follow-up

Adverse effects of imiquimod treatment: patient reported side effects and side effects noticed at clinical investigation.

#### 26 weeks follow-up

##### Imiquimod group

Cervical cytology and HPV genotype.Quality of lifeDetermination of grade of cervical dysplasiaTreatment compliance: amount of applied doses of imiquimod.Adverse effects of imiquimod treatment: patients reported side effects and side effects noticed at clinical investigation.

##### LLETZ group

Cervical cytology and HPV genotype.Quality of lifeWith abnormal PAP smear, determination of grade of cervical dysplasia.

#### 12 and 24 months follow-up

Cervical cytology outcomes for all treatment groups, including HPV genotyping.

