### Interventions

Patients will receive verbal and written information about the study procedure. They have to sign an informed consent, where after patients are randomized into the intervention arm or the standard treatment:Intervention arm: Imiquimod treatment. Patients in this group have to insert imiquimod 5% cream intravaginally for 16 weeks.Standard treatment. A LLETZ procedure is performed according to the current guidelines.

Patients in the imiquimod treatment group will apply imiquimod 5% cream intravaginally during 16 weeks. One sachet contains 12,5 mg of imiquimod and is applied with a vaginal applicator. The application frequency is 3 times a week. Patients get instructions and administer the cream themselves, before bedtime. The patients are advised to take an intravaginal shower with an applicator the next morning in order to remove cream leftovers, followed by an external shower to remove any remains on the vulva. Anti-inflammatory drugs (paracetamol or NSAID) can be used in case of mild systemic drug-related side effects. If the local or systemic side effects persist or are severe, patients are advised to reduce the frequency of the imiquimod insertion, first twice weekly, subsequently once weekly. Imiquimod treatment is discontinued for maximum of a week in case of persistent side effects. In order to prevent pregnancy, patients are advised to use adequate contraception. Subjects should refrain from vaginal sexual intercourse during the nights that imiquimod is applied until the vaginal shower the next morning. After 10 weeks a colposcopy is performed to rule out disease progression. Biopsies are only performed in case of suspicion of invasive disease.

In the standard treatment group, patients will undergo a LLETZ procedure within 4 weeks after the diagnosis. Excision of macroscopic lesions and the transformation zone will be achieved by a monopolar loop electrode, preferably under local anaesthesia.

Treatment efficacy is evaluated at 26 weeks follow-up for both groups. The Imiquimod group will have a Pap smear and a colposcopy with diagnostic biopsies. Biopsies are performed at the initial CIN lesion site and at any other suspect site, with a minimum of two. In case of persistent or progressive disease, surgical excision is performed. The LLETZ group will have follow-up with cervical smears at 6, 12 and 24 months according to the current guidelines.

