### Statistical methods

Analysis will be done according to the intention to treat principle and the non-inferiority principle to show that imiquimod is not worse than an existing treatment (LLETZ). To investigate efficacy we will perform a per protocol analysis (although this is not the primary outcome of the study). The primary outcome is the difference between the probability of regression in the LLETZ and the imiquimod arms. The expected difference (LLETZ-imiquimod) will be calculated together with the 95% Aggresti confidence interval. If the upper bound of the interval lies below the non-inferiority margin of 10% non-inferiority of the imiquimod treatment is assumed to be proved. Logistic analysis of potential confounders (age at diagnosis, CIN grade, number of previous treatments, smoking, HPV-subtype) will be performed. Analysis will be based on intention to treat protocol.

The prevalence and severity of side effects of imiquimod and LLETZ treatment, as documented according to Common Terminology Criteria for Adverse Events guidelines, will be presented as proportions and means with 95% confidence intervals. Differences in the rates of overall side-effects and severe side-effects between the imiquimod and LLETZ groups will be tested with a chi-square test. Disease recurrence rates, defined by abnormal cervical cytology, after 6, 12 and 24 months will be evaluated in adequately treated patients by use of multiple logistic regression analysis, after adjustment for age at diagnosis, CIN grade, smoking sexual behavior and HPV subtype.

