## Discussion

The development of a non-surgical treatment modality for residual and recurrent CIN lesions will lower the amount of LLETZ procedures for this indication and complications as a result of surgical intervention. Evidence shows that 15–22% of high-grade CIN lesions will persist or recur after 2 years and that patients after treatment for high grade CIN lesions will remain at higher risk for cervical cancer in the future. Based on earlier studies, we hypothesize that at least 50% of patients with high grade CIN will benefit from immunotherapy with imiquimod. The current study aims to test the treatment effectivity, while also assessing the clinical applicability of imiquimod treatment by documentation of side effects and quality of life associated with treatment.

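### No scheduled side-effect record covers excisions after week 26, so surgical complications of the imiquimod strategy are under-collected; the net effect on the overall side-effect comparison is unknown

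*Protocol article*

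**What the plan says.** The Interventions section of the protocol article makes surgery part of the imiquimod strategy after the week-26 biopsies: "In case of persistent or progressive disease, surgical excision is performed". The Abstract names the procedure as a LLETZ. The section on withdrawal adds that withdrawn women will in principle also have one.

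The Data collection section then lists, visit by visit, what is recorded. For LLETZ side effects there is one item, at 6 weeks: "Adverse effects of LLETZ treatment: patient reported side effects". In the imiquimod arm the last side-effect item is at week 26, and it is limited to the study drug: "Adverse effects of imiquimod treatment: patients reported side effects and side effects noticed at clinical investigation". For 12 and 24 months the list reads: "Cervical cytology outcomes for all treatment groups, including HPV genotyping".

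The incidence and severity of side effects of both treatments is a secondary objective. The Statistical methods section fixes the comparison: "Differences in the rates of overall side-effects and severe side-effects between the imiquimod and LLETZ groups will be tested with a chi-square test". It does not say whether events after a rescue excision count. The Ethical considerations section says in general terms that adverse events will be recorded and reported, without an end date, and that a safety board is in place for the whole study.

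**The concern.** The trial is motivated by sparing women the complications of a repeat LLETZ. A woman in whom imiquimod fails bears the side effects of the cream and then those of the excision. The second part falls after the last listed side-effect record in her arm, and that record asks only about imiquimod. A woman allocated to LLETZ is asked about the same kind of complication 6 weeks into the study.

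The same procedure is therefore followed by a solicited side-effect report in one arm and by none in the other. At stake is whether the trial can say how much surgical morbidity the imiquimod strategy really avoids. Events not asked about at the time cannot be recovered reliably later.

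**Working it through.** **Schedule, arm by arm (Data collection)**
- Week 6: imiquimod by patient report and clinical examination; LLETZ by patient report only.
- Weeks 10 and 16: imiquimod by both methods; nothing listed for LLETZ.
- Week 26: imiquimod by both methods, for effects of imiquimod; nothing listed for LLETZ.
- Months 12 and 24: no side-effect item in either arm.

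That is four scheduled records against one. Treatment lasts 16 weeks and the biopsy follows 10 weeks later (16 + 10 = 26). The excision depends on the biopsy result, so it comes after the week-26 record.

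**Inputs (Sample size calculation, Discussion)**
- Regression: "we assume that the probability of regression is 63% for the standard (LLETZ procedure) while it is 60% after treatment with imiquimod". Non-regression is therefore 1 − 0.60 = 0.40 with imiquimod and 1 − 0.63 = 0.37 with LLETZ.
- 174 evaluable per group; 433 randomised, so 433 / 2 = 216.5 per arm, with 20% allowed for loss.
- The Discussion is less optimistic for high-grade disease: "we hypothesize that at least 50% of patients with high grade CIN will benefit from immunotherapy with imiquimod". That allows up to 50% failure.

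**The plan's own figure.** The plan gives no count of rescue excisions. Its 174 per group comes out as (0.63 × 0.37 + 0.60 × 0.40) × (1.645 + 0.842)² / 0.13² = 173.1, rounded up, and 2 × 173.08 / 0.8 = 432.7, rounded to 433. The 0.13 is 0.10 + 0.03. With the stated direction of the difference the divisor would be 0.07², giving 597 per group. That is a separate matter. It leaves the 40% unchanged, but the counts below would scale with the arm size.

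**Expected excisions after week 26, imiquimod arm**
- Evaluable women: 0.40 × 174 = 69.6, about 70.
- At the Discussion's 50%: 0.50 × 174 = 87.

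**Complications without scheduled collection.** The article gives no complication rate. Let c be the risk per excision; c = 5% to 30% is an assumption for illustration.
- Imiquimod arm: 0.40c per woman, or 2 to 12 per 100 women. In 174 women this is 69.6 × 0.05 = 3.5 to 69.6 × 0.30 = 20.9 events.
- LLETZ arm, if every failure is re-excised: 0.37c per woman, from about 0.37 × 174 = 64 women.

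**Effect on the comparison of LLETZ complications only**
- If all failures in both arms are excised, the expected number per woman is c + 0.37c = 1.37c in the LLETZ arm, of which c is solicited (0.37 / 1.37 = 27% not). In the imiquimod arm it is 0.40c, of which none is solicited. The true ratio is 0.40 / 1.37 = 0.29; the schedule would show zero. On the difference scale the error is only 0.40c − 0.37c = 0.03c (0.15 to 0.9 percentage points).
- If only imiquimod failures are excised, the true ratio is 0.40, the schedule again shows zero, and the error in the difference is the full 0.40c.

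**The case against.** A reader might infer that rescue-LLETZ complications are never counted. The documents do not support that. The general adverse event statement has no end date and is not limited to the study drug, so such events may well be recorded. What stands is narrower: the statement sets no contact after a rescue excision and does not say that such events enter the group comparison.

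A reader might also infer that the safety comparison as a whole favours imiquimod. That is not established either. The imiquimod arm is questioned at four visits and examined clinically each time, which raises its recorded rate against a single patient-reported contact. Any re-excision of the assumed 37% failures in the LLETZ arm is equally unscheduled. If the chi-square counts women with any side effect, a rescue complication changes the result only for a woman with none recorded before. These features work against, or dilute, the bias from missed rescue complications, and nothing in the article shows where the balance falls.

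The count should not be pushed either. Applying 40% to all randomised women gives 0.40 × 216.5 = 87, but that includes women the plan allows for as lost. Moreover, the primary outcome is cytological, whereas biopsy triggers the excision, and CIN 1 to 3 is eligible, so failure and rescue need not coincide.

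Finally, an article condenses the full protocol, and the list is not complete in every respect: quality of life at one year is named among the objectives but not under the 12-month visit. Side effects could likewise have been left out. Against this, the article chose to list side-effect items visit by visit and by arm. Followed as written, that list gives an unequal collection rule rather than mere silence. The comparison could also be read as one of treatments rather than strategies, but the test is stated between the two groups, and the plan itself prescribes the second procedure in one of them.

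**Conclusion.** The point holds in limited form. The listed schedule has no side-effect item after week 26 in the imiquimod arm or after week 6 in the LLETZ arm, although the plan itself expects about 70 of 174 evaluable imiquimod patients to reach an excision after week 26. That number rests on the 60% planning rate and on treating non-regression as a rough stand-in for biopsy-triggered rescue.

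For surgical complications, the burden of the imiquimod strategy is understated by up to 0.40c per woman. Under the planning rates, the difference between arms shifts in favour of imiquimod by between 0.03c and 0.40c, depending on how many LLETZ failures are re-excised. For the overall side-effect test the net direction is unknown.

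This affects a secondary objective, not the primary outcome. It should be corrected because the missing complications are the ones the trial sets out to avoid.

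**What to change.** In Data collection, apply the existing 6-week patient-reported LLETZ side-effect record after every excision performed in either arm up to 24 months, whether it follows the week-26 assessment, a withdrawal or a later abnormal result.

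In Statistical methods:
- report side effects by randomised arm with these excisions included;
- show the initial-treatment phase separately;
- state that the arms differ in the number and method of side-effect assessments, so that the overall chi-square result is read with that in mind.

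The cost is one short contact per later excision: about 70 in the imiquimod arm, and up to about 64 in the LLETZ arm if every assumed failure is re-excised. One extra table is needed. No treatment or procedure changes. The result may become less favourable to imiquimod. A 6-week contact will not capture later fertility or pregnancy outcomes, and the report should not suggest that it does.
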